## Abstract

**Background:**

The coronavirus disease 2019 (COVID-19) caused by severe acute respiratory syndrome coronavirus-2 (SARS-CoV-2) has led to a significant number of mortalities worldwide. COVID-19 poses a serious threat to human life. The clinical manifestations of COVID-19 are diverse and severe and 20% of infected patients are reported to be in a critical condition. A loss in lung function and pulmonary fibrosis are the main manifestations of patients with the severe form of the disease. The lung function is affected, even after recovery, thereby greatly affecting the psychology and well-being of patients, and significantly reducing their quality of life.

**Methods:**

Participants must meet the following simultaneous inclusion criteria: over 18 years of age, should have recovered from severe or critical COVID-19 cases, should exhibit pulmonary fibrosis after recovery, and should exhibit Qi-Yin deficiency syndrome as indicated in the system of traditional Chinese medicine (TCM). The eligible candidates will be randomized into treatment or control groups. The treatment group will receive modern medicine (pirfenidone) plus TCM whereas the control group will be administered modern medicine plus TCM placebo. The lung function index will be continuously surveyed and recorded. By comparing the treatment effect between the two groups, the study intend to explore whether TCM can improve the effectiveness of modern medicine in patients with pulmonary fibrosis arising as a sequelae after SARS-CoV-2 infection.

**Discussion:**

Pulmonary fibrosis is one of fatal sequelae for some severe or critical COVID-19 cases, some studies reveal that pirfenidone lead to a delay in the decline of forced expiratory vital capacity, thereby reducing the mortality partly. Additionally, although TCM has been proven to be efficacious in treating pulmonary fibrosis, its role in treating pulmonary fibrosis related COVID-19 has not been explored. Hence, a multicenter, parallel-group, randomized controlled, interventional, prospective clinical trial has been designed and will be conducted to determine if a new comprehensive treatment for pulmonary fibrosis related to COVID-19 is feasible and if it can improve the quality of life of patients.

*Trial registration:* This multicenter, parallel-group, randomized controlled, interventional, prospective trial was registered at the Chinese Clinical Trial Registry (ChiCTR2000033284) on 26th May 2020 (prospective registered).

[figure not shown]

## Background

Coronavirus disease-2019 (COVID-19) was discovered in December 2019, it has resulted in a sudden and significant number of hospitalizations and pneumonia-related deaths globally to date [1–3]. COVID-19 is associated with morbidity and mortality globally and has been defined as an “international emergency” and characterized as a pandemic by the World Health Organization (WHO) [1]. Currently, this infection is prevalent in more than 215 countries. As of February 21, 2021, over 111.07 million confirmed cases and 2.46 million deaths resulting from COVID-19 have been reported globally [4]. The rapid spread of COVID-19 poses significant economic, social, and healthcare challenges worldwide.

The causative organism of COVID-19 is the severe acute respiratory syndrome coronavirus-2 (SARS-CoV-2) [1, 2, 5]. Epidemiological data suggests that droplet transmission is the most common transmission route and that surface contact is another important mode of transmission [6]. Patients are the most important source of transmitting infection [7, 8]. Additionally, asymptomatic patients may play a role in transmission and should not be neglected [9].

COVID-19 can lead to a wide spectrum of respiratory diseases with an extremely high incidence of acute respiratory distress syndrome. It has various clinical manifestations [9], ranging from asymptomatic infections to mild respiratory tract disease and severe interstitial pneumonia, which may lead to respiratory failure and death [6]. About 81% of patients with COVID-19 exhibit mild symptoms [7], characterized by fever, fatigue, and dry cough. A few patients with mild infection show signs of nasal congestion, runny nose, sore throat, and diarrhea [7], whereas none of the mild cases exhibit pulmonary inflammation upon imaging. Patients with the mild form of the infection recover completely within 1–2 weeks. However, 19% of patients with COVID-19 exhibit severe manifestations [7], including respiratory failure, septic shock, and multiple-organ dysfunction, it is characterized by progressive dyspnea and intractable hypoxemia. These conditions are difficult to treat and can prove to be fatal in the absence of prompt and specific medical treatment [7].

Currently, there are no specific or effective options (including remdesivir, convalescent and plasma therapy) to treat severe or critical COVID-19 cases [11–13], some comprehensive treatment methods were used to treatment those fatal cases fact to experience principle, the therapy methods involved using antivirals, antibiotics, hormones, and mechanical ventilation [14–16]. Although most patients can be cured, a small number of patients may exhibit lung injury after recovery [17] and pulmonary fibrosis is one of the sequelae of COVID-19 [18, 19]. This progressive disease is characterized by a significant decrease in lung function, which cause respiratory failure and death. The common clinical manifestations of pulmonary fibrosis are dyspnea and deterioration of the lung function index. Currently, lung transplantation is the only viable treatment option that is known to improve outcomes [20]. Moreover, the recovery of pulmonary function is a slow process [21, 22] and patients may experience several drug-induced side effects [21, 22]. Hence, both the mental and physical functions of patients are greatly affected, along with a considerable decline in the quality of life. The burden of fibrotic lung disease following SARS-CoV-2 infection is likely to be high, and the global burden is likely to further increase, considering the steady rise in the number of individuals afflicted with COVID-19 [21].

There is evidence that drugs, such as pirfenidone and nintedanib, can delay the decline of lung function in patients with pulmonary fibrosis [23]. However, the natural course of pulmonary fibrosis is irreversible. Drug therapy using antifibrotic agents may be beneficial in the treatment of COVID-19 through a range of mechanisms, and prevent long-term adverse consequences. Traditional Chinese medicine (TCM) has been commonly used in the prevention of fibrosis and improvement of lung function [24–26].

Parallel, double-blind, multicenter, randomized clinical trials (RCTs) constitute a reliable method for evaluating drug efficacy. It is hypothesized that the integration of TCM and modern medicine may be effective in the treatment of pulmonary fibrosis caused by COVID-19. Based on this combination, a new treatment for pulmonary fibrosis may be obtained, it may significantly improve the life expectancy of patients with pulmonary fibrosis caused by COVID-19 (Fig. 1).

**Fig. 1 Fig1:**
[figure not shown]
The technology roadmap of this study. *COVID-19* Corona Virus Disease 2019, *SARS-CoV-2* Severe acute respiratory syndrome coronavirus 2, *SAS* Self-rating anxiety scale, *SCL-90* Symptom self-evaluation scale; *SDS* Self-rating depression scale, *SF-36* 36-Item short form health survey, *TCM* Traditional Chinese medicine;

### Aim of the study

This multicenter, parallel, double-blind RCT will be conducted in a clinical setting. Patients who recovered from severe and critical COVID-19 and subsequently developed pulmonary fibrosis will be recruited for this study. Additionally, all subjects will have Qi-Yin deficiency TCM syndrome. The enrolled subjects will be divided randomly into the treatment or control group. Subjects in the treatment group will receive modern medicine plus TCM, whereas those in the control group will be provided modern medicine plus a TCM placebo. The lung function index and quality of life score will be continuously examined for each participant. By comparing the treatment effect between the two groups, we will explore whether TCM can improve the effectiveness of modern medicine when used to treat pulmonary fibrosis induced by COVID-19. There are several outcomes that we will evaluate from this study. First, we will discover the basic characteristics of pulmonary fibrosis related to COVID-19. Second, we will explore the risk factors of pulmonary fibrosis-related COVID-19 that could provide references for the identification of COVID-19. Third, we will determine the influencing factors that could improve the outcomes of pulmonary fibrosis-related COVID-19. Fourth, we will compare the efficacy of modern medicine + TCM versus modern medicine + TCM placebo, it can help screen and optimize a novel comprehensive treatment approach for effectively improving the outcome and quality of life of patients with induced by COVID-19.

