##### Inclusion criteria

Patients who meet all the following inclusion criteria may be included in the clinical trial:Diagnostic criteria for severe or critical COVID-19Patients exhibiting positive etiological evidence of the SARS-CoV-2 nucleic acid determined using real-time polymerase chain reaction (PCR) or gene sequencing will be included. In addition, patients should meet at least one of the following diagnostic criteria of severe COVID-19. First, shortness of breath and a respiratory rate (RR) ≥ 30 times/min. Second, oxygen saturation (SpO_2_) in quiescent condition ≤ 93% using finger measurement. Third, arterial partial pressure of oxygen (PaO_2_)/oxygen inhalation concentration (FiO_2_) ≤ 300 mmHg (1 mmHg = 0.133 kPa). The PaO_2_/FiO_2_ will be recalculated when patients will be enrolled from regions at high altitudes, especially those located 1000 m above sea level, using the following formula: PaO_2_/FiO_2_ × [atmospheric pressure (mmHg) /760].The diagnostic criteria of critical COVID-19 should meet one of the following criteria, including respiratory failure and those who needed mechanical ventilation, shock, or respiratory failure combined with organ failure, which required monitoring and treatment in an intensive care unit (ICU).Diagnostic criteria for pulmonary fibrosisThe diagnosis criteria of pulmonary fibrosis will be in accordance with the guidelines of evidence-based medicine (2011 Edition) of the ATS, European Respiratory Society (ERS), Japanese Respiratory Society (JRS), and the Latin American Thoracic Association (ALAT).The inclusion criteria for patients with pulmonary fibrosis should meet one of the following conditions. First, subjects should present diffuse, asymmetric reticular formation in the lungs. Second, the reticular formation should show nodular shadows in a lung X-ray and there should be reticular shadows in the lower lobes of both lungs, especially under the pleura. Third, subjects should exhibit restrictive ventilation dysfunction, decreased lung volume, functional residual volume, and normal or increased forced lung volume (FLV)/ forced expiratory volume in 1 s(FEV1) upon assessing lung function. In addition, they should exhibit decreased carbon monoxide(CO) levels exhaled in the single-breath determination of CO. Open chest or thoracoscopic lung biopsy will be considered the “gold standard" for the diagnosis of pulmonary fibrosis.In this study, the pulmonary function indices must meet the following criteria. First, the predicted forced vital capacity (FVC%) must be between 50 and 90%. Second, the diffusion capacity for carbon monoxide (DLCO) should be between 30 and 90%. Third, the FEV1/forced vital capacity(FVC) must be over 80%. Fourth, when subject is at rest in a room and is respiring normally, the oxygen partial pressure should more than 50 mmHg.TCM syndrome differentiation for subjectsThe criterion of TCM syndrome differentiation complies with TCM disease diagnosis and efficacy standards promulgated by the China State Administration [32]. In addition, the criterion of Qi-Yin deficiency must meet the following criteria, including shortness of breath, cough, sputum expectoration, a small amount of yellow and white sputum, spontaneous sweating, night sweats, fatigue, drawl, dry mouth, afternoon hot flashes, hot facial flashes, anorexia, red tongue, thin white coating on the tongue, and weak pulse[32]. Qi-Yin deficiency was found to account for 41.5% (39/94) of all individuals with pulmonary fibrosis in other studies[33].Age: ≥ 18 yearsWritten informed consent must be obtained from the patient or from their legal guardian. Patient may also be enrolled upon confirmation of the urgency of participation in the clinical trial and the possible benefit to the patient assessed by an independent consultant, or the implementation of other established procedures to include patients who are unable to provide informed consent.

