#### Investigational drug

##### Therapeutic schedule

In this study, TCM experts will identify and select the research subjects with Qi-Yin deficiency based on TCM syndrome differentiation, while experts in modern medicine will formulate the drug prescription and design a treatment plan. All subjects will be randomly divided into a treatment or control group in a 1:1 ratio. The treatment group will receive modern medicine + TCM herb granule 1, while the control group will be treated using modern medicine + TCM herb granules (placebo). During treatment, the dosage of the TCM herb or pirfenidone was not adjusted for any subject.

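### On its natural reading, the second aim (risk factors for COVID-19 pulmonary fibrosis) cannot be met, because every participant must already have fibrosis and confirmed COVID-19

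*Protocol article*

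**What the plan says.** Aim of the study gives as its second aim "we will explore the risk factors of pulmonary fibrosis-related COVID-19". The sentence in full is "Second, we will explore the risk factors of pulmonary fibrosis-related COVID-19 that could provide references for the identification of COVID-19". The third aim follows as a separate item: "Third, we will determine the influencing factors that could improve the outcomes of pulmonary fibrosis-related COVID-19".

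The same section defines who is recruited: "Patients who recovered from severe and critical COVID-19 and subsequently developed pulmonary fibrosis will be recruited for this study". The Methods part of the Abstract lists, among criteria that must hold together, that participants "should exhibit pulmonary fibrosis after recovery".

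Inclusion criteria opens with "Patients who meet all the following inclusion criteria may be included in the clinical trial". One of those required items is pulmonary fibrosis, introduced by "The inclusion criteria for patients with pulmonary fibrosis should meet one of the following conditions". Another is positive nucleic acid or sequencing evidence of SARS-CoV-2 together with severe or critical disease.

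Therapeutic schedule describes the only groups in the study: "All subjects will be randomly divided into a treatment or control group in a 1:1 ratio".

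**The concern.** A risk factor for developing a condition is found by comparing people who developed it with people who did not. Here the condition is an entry requirement, so the second group is missing. The section on information collected after enrolment nevertheless sets out a long list of exposures and past COVID-19 treatments, so the raw material for a table of apparent risk factors will exist.

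What is at stake is the claim the trial can make. The frequency of an exposure among selected cases is descriptive. Without fibrosis-free survivors it carries no information on whether that exposure raises the chance of fibrosis. Limitations of this study does not mention this.

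**Working it through.** The plan gives no figure for this aim, so the check sets the aim against the design and asks whether the quantity it needs can be estimated.

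**Step 1. Does fibrosis vary among participants?** Sample size calculation gives 257 per group, so 2 × 257 = 514 planned participants. The Abstract, Aim of the study and Inclusion criteria all require fibrosis. Participants with fibrosis at entry: 514. Participants without: 0.

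**Step 2. Is an association with fibrosis estimable?** For any exposure, let a and b be the exposed and unexposed participants with fibrosis, and c and d the exposed and unexposed participants without it.
- By the entry rule, a + b = 514 and c = d = 0.
- Odds ratio = (a × d)/(b × c) = 0/0, undefined.
- Risk among the exposed = a/(a + c) = a/a = 1, and among the unexposed = b/(b + d) = b/b = 1. The ratio is 1 for every exposure present in some but not all participants. That is a product of selection and not a finding.
- The one quantity available is a/514, the frequency of the exposure among eligible cases.

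None of this depends on the size of the trial.

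**Step 3. Does the stated purpose, identifying COVID-19, fare better?** No. SARS-CoV-2 infection must be proven in every participant, so COVID-19 status does not vary either.

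**Step 4. Does another section supply a comparison group?**
- Study setting speaks more broadly of lung function damage, with fibrosis as one kind. It does so when explaining the choice of hospitals, and it does not relax the inclusion rule.
- Covariates are collected from enrolled participants only, and the declared use of the questionnaire is to study what affects efficacy and outcome.
- The Statistical analysis sections compare the two randomised arms and adjust for centre and confounders. None analyses the occurrence of fibrosis.

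**Step 5. Could an outside fibrosis-free series be borrowed?** Not cleanly. The cases are also selected on Qi-Yin deficiency and on ranges for FVC% and DLCO. Several exposures on the questionnaire (tuberculosis, HIV/AIDS, COPD, lung cancer, tumours) are grounds for exclusion. Glucocorticoid or immunosuppressant use in the past 3 months is also an exclusion, while past use of both is to be recorded as an exposure.

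**The case against.** The strongest reply is that the sentence never says factors for *developing* fibrosis. It is poorly written, and it could mean factors for a worse course among patients who already have fibrosis. Primary outcome defines deterioration as its own level, and the questionnaire is declared to serve efficacy and outcome. On that reading the outcome varies and odds ratios can be estimated. Improvement and deterioration are also different ends of the scale, so the overlap with the third aim need not be complete.

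Part of this stands. The wording does not have one certain meaning, so the conclusion is tied to the natural reading. But the within-cohort reading is strained. It leaves the identification clause without a function, it overlaps the third aim, and Data analysis of the main outcome measure merges deterioration with stabilisation, so no planned primary analysis isolates it.

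It may also be said that this is a condensed article and that a fuller document could describe a comparison source. That calls for some caution. An analysis plan alone, however, cannot restore variation that eligibility has removed, and the groups shown are the two randomised arms.

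A last reply is that the aim is only exploratory. That excuses low precision or many tests. It does not help when the outcome is constant.

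Two stronger inferences should be resisted. A reader might infer that risk factors will in fact be reported from these cases alone. The documents announce no such analysis, so this is a foreseeable risk and no more. A reader might also infer a flaw in the trial as a whole. The aim feeds no endpoint, sample size input or specified test.

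**Conclusion.** The point holds in a limited form. On its natural reading the second aim cannot be met: fibrosis is present in 514 of 514 planned participants by design, confirmed COVID-19 likewise, and no fibrosis-free group is described. The stated purpose of identifying COVID-19 fails for the same reason.

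This rests on two assumptions: that the aim refers to the occurrence of fibrosis, and that no comparison cohort exists outside the article. It would be too strong to say that the aim is impossible under every reading, since associations with deterioration or severity within the cohort can be estimated.

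The randomised comparison, the primary outcome and the safety assessment are untouched, and the third aim can be addressed with the planned data. The point concerns what the trial may claim, and it should be corrected because the correction costs almost nothing.

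**What to change.** Either of two changes to Aim of the study would do.

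1. Delete the second aim and leave prognostic factors to the third.
2. Restate it as an exploratory analysis within the enrolled patients, with a named outcome that varies. Examples are deterioration as defined under Primary outcome, or severity at baseline. Drop the clause on identifying COVID-19. State that results are associations conditional on the eligibility criteria and are not risk factors for developing fibrosis.

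If deterioration is chosen, the three-level classification has to be kept for this analysis, because the primary analysis merges it with stabilisation. The article gives no expected frequency of deterioration, so the precision of such an analysis cannot be judged from it.

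If baseline FVC% or DLCO is chosen, state that Inclusion criteria truncates them at 50–90% and 30–90%. Selecting on the outcome in this way will distort the associations.

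The cost is about one sentence of wording, with no change to sample size, visits or data collection. The small downside is giving up one advertised exploratory aim.

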### Hypothesis

Some studies have reported that TCM can significantly reduce the severity of pulmonary fibrosis induced by several factors, including pathogens [27, 28]. The efficacy of TCM in improving lung function has also been established partly [27, 28]. In addition, some studies have found that the combination of modern medicine and TCM is effective in improving lung function and the quality of life of patients compared to therapy using modern medicine and/or TCM placebo [29, 30]. Hence, it was hypothesized that Using modern medicine (Pirfenidone) with TCM may promote lung function in subjects who recovered from severe or critical COVID-19. Thus, the study will likely provide novel insights into the long-term outcomes of COVID-19 in this category of patients.

### Research methods/design

#### Ethical aspects of the study

This study has been approved by the Chinese Clinical Trial Registry (ChiCTR2000033284) and the ethical review committee of Guangzhou Women and Children’s Medical Center Research Ethics Committee (No.202028500). All experimental procedures will be performed in accordance with the declaration of Helsinki and written informed consent will be obtained from all participants following a detailed description of the purpose, potential risks, and benefits of the study. Participation will be voluntary and will be offered the choice to withdraw from the study at any time without any obligations.

##### Study setting

The study will be carried out in provinces where the prevalence of COVID-19 was high, thereby comprising a large pool of patients with severe and critical COVID-19. Several hospitals will be selected, as it is likely that several patients with lung function damage (including pulmonary fibrosis) related to COVID-19 will be enrolled. In addition, only physicians in these hospitals who are experienced in the treatment of respiratory diseases will be recruited. Moreover, these physicians will be trained in the aspects of the theory and principle of TCM, such that the research team can function collaboratively and seamlessly.

